### Interim analyses {21b}

N/A. No other interim analyses are planned.

### Methods for additional analyses (e.g., subgroup analyses) {20b}

We will conduct a cost-effectiveness analysis and a cost-utility analysis with the incremental cost-effectiveness ratio (ICER) and the incremental cost-utility (ICUR) as the primary economic outcomes [62]. The ICER represents the difference between the mean cost of the HC intervention compared with the ED program, divided by the difference in mean effectiveness (measured by the SPPB), where the ICER = ∆ Cost/∆ SPPB (where a change of 0.5 in the SPPB score is clinically meaningful). The ICER represents the difference between the mean cost of the HC intervention compared with the ED, divided by the difference in mean utility (measured by QALYs), where the ICUR = ∆ Cost/∆ QALY. QALYs will be estimated using the EQ-5D-5L and area under the curve analysis. We will determine the incremental cost per mean change in QALYs estimated from the EQ-5D-5L of HC versus ED. This economic evaluation will use a 26-week time horizon that aligned with intervention cessation and 52 weeks that aligns with the 26-week follow-up. The economic evaluation will be completed using two perspectives, the health care system and societal [62].

We will perform a subgroup analysis including the interaction term of biological sex by experimental group (sex x group) to account for possible effects of sex on the outcomes of the intervention. Outcomes will also be analyzed by gender by including the interaction term of gender identity, using the Gender Identity Scale [24], by experimental group (gender x group).

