### Outcomes {12}

#### Descriptors

We will collect information on key descriptors including general health, biological sex, current medication use, education, and socioeconomic status via interview and questionnaires. Resting vital signs, heart rate and blood pressure, will be measured with an automatic sphygmomanometer, the Omron HEM-775 in a seated position prior to physical assessments. Body mass index will be calculated as mass in kg/height in m [2]. Comorbidity with physical function will be determined by the Function Comorbidity Index [22]. Functional status will be assessed using the Lawton-Brody Instrumental Activities of Daily Living (IADL) Scale [23]. Gender-related characteristics will be assessed using questionnaires about gender identity (Gender Identity Scale) [24] and institutional gender (income, education level). The Gender Identity Scale offers three gender identities: female/woman/girl, male/man/boy, and other gender(s) [24].

All outcomes will be assessed at baseline, 13 weeks (mid-point), 26 weeks (final), and 52 weeks (follow-up). The following secondary outcomes will also be collected midway through the follow-up period at 39 weeks via phone call: fatigue, community mobility, mood, health-related quality of life, and sleep.

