## Statistical methods

### Statistical methods for primary and secondary outcomes {20a}

All primary and secondary analysis will follow the intent to treat principle. Participants who have been randomized will be included in all analysis to estimate intervention effects irrespective of deviations from the intervention protocol [61]. The primary outcome (SPPB) will be modeled using a three-level linear mixed model that includes random intercepts at the coach and the participant levels (for the HC group) or the education cohort and the participant levels (for the ED group), fixed effects of time, experimental group (HC vs. ED), and the group-by-time interactions. The treatment effect will be estimated as the difference in mean change in outcome between the two arms, calculated using the fitted model coefficients. Secondary outcomes will be analyzed using analogous linear mixed models. All linear mixed models will be adjusted for baseline outcome score and baseline characteristics. The proportion of participants able to complete the 400-m walk at trial completion and at 6-month follow-up will be compared using a two-level (clusterd by coach in the HC group, clusterd by cohort in the ED group) logistic mixed model for binary outcomes. A pre-specified statistical analysis plan will be developed prior to the release of data for analysis.

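### The ICUR denominator is a difference in mean area-under-the-curve QALYs with no adjustment for baseline EQ-5D-5L utility stated; adding it would gain precision at no cost

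*Protocol article*

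**What the plan says.** All references are to the protocol article.

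- **Methods for additional analyses {20b}** makes the ICUR one of two primary economic outcomes. Its numerator is the difference in mean cost, "divided by the difference in mean utility (measured by QALYs"). On construction: "QALYs will be estimated using the EQ-5D-5L and area under the curve analysis". A further sentence words the contrast differently: "We will determine the incremental cost per mean change in QALYs estimated from the EQ-5D-5L of HC versus ED". On horizons: "This economic evaluation will use a 26-week time horizon that aligned with intervention cessation and 52 weeks that aligns with the 26-week follow-up". Baseline utility, covariates and a regression model are not mentioned.
- **Statistical methods for primary and secondary outcomes {20a}** holds the only rule on baseline adjustment: "All linear mixed models will be adjusted for baseline outcome score and baseline characteristics". The same section adds: "A pre-specified statistical analysis plan will be developed prior to the release of data for analysis".
- **Outcomes {12}, Descriptors** gives the visits: "All outcomes will be assessed at baseline, 13 weeks (mid-point), 26 weeks (final), and 52 weeks (follow-up"), with an extra collection at "39 weeks via phone call: fatigue, community mobility, mood, health-related quality of life, and sleep". The section on health-related quality of life names the EQ-5D-5L as its instrument, so baseline utility is available.

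**The concern.** Baseline utility is the first point of the area under the curve and is correlated with every later point. If the arms differ at baseline by chance, an unadjusted difference in mean QALYs inherits part of that gap.

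The rule in {20a} does not settle the matter. It covers linear mixed models of repeated measures and adjusts for the baseline value of the outcome. A QALY by area under the curve is one number per participant with no baseline value of its own, so the covariate has to be named as baseline EQ-5D-5L utility. The rule would cover EQ-5D-5L as a secondary outcome, but that is not the ICUR denominator.

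The two wordings in {20b} add a second uncertainty. A difference in mean QALYs and a mean change in QALYs could be the same contrast between arms, or the latter could mean a change from baseline. These treat baseline utility differently. At stake are the precision of a primary economic outcome and the freedom to choose between versions of it after the data are seen.

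**Working it through.** **Plan's own figures.** The article states no figure for the QALY difference. The sample size it does state reproduces: the unrounded effect size (1.1915 − 0.84)/0.98 = 0.3587 gives 123 per group, 246 in total, and 246/0.85 = 289.4, rounded up to 290. I use 123 per group as the number expected to complete.

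**Inputs from the article.** Utility at 0, 13, 26, 39 and 52 weeks; horizons of 26 and 52 weeks.

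**Assumptions, not in the article.** Utility SD 0.15 (range 0.10-0.20); the same SD at every visit; equal correlation ρ between all visits, 0.5-0.8.

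**Trapezoid weights in years.**
- 26 weeks: w = (0.125, 0.25, 0.125); sum 0.5; sum of squares 0.09375.
- 52 weeks: w = (0.125, 0.25, 0.25, 0.25, 0.125); sum 1; sum of squares 0.21875.

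**Slope of QALY on baseline utility.** β = w₀ + ρ × (sum of the other weights).
- 26 weeks: 0.125 + 0.375ρ = 0.3125 to 0.425.
- 52 weeks: 0.125 + 0.875ρ = 0.5625 to 0.825.

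**Share of variance removed by adjustment.** V = (1 − ρ)Σw² + ρ(Σw)², in units of SD²; share = β²/V. The SD cancels.

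| Horizon | ρ | V | β² | Share removed |
|---|---|---|---|---|
| 26 weeks | 0.5 | 0.1719 | 0.0977 | 57% |
| 26 weeks | 0.8 | 0.2188 | 0.1806 | 83% |
| 52 weeks | 0.5 | 0.6094 | 0.3164 | 52% |
| 52 weeks | 0.8 | 0.8438 | 0.6806 | 81% |

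On the SE scale, the adjusted SE is 0.66 to 0.42 of the unadjusted SE at 26 weeks and 0.69 to 0.44 at 52 weeks. With SD 0.15 and ρ = 0.7, the SE falls from 0.0086 to 0.0044 at 26 weeks and from 0.0167 to 0.0090 at 52 weeks.

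**What a baseline imbalance carries.** The SE of the baseline difference is SD × √(2/123) = 0.15 × 0.1275 = 0.0191 (0.0128-0.0255 for SD 0.10-0.20). An imbalance of one SE shifts the unadjusted QALY difference by β × 0.0191:
- 26 weeks: 0.0060 to 0.0081 (0.0040 to 0.0108 over the whole SD range).
- 52 weeks: 0.0108 to 0.0158 (0.0072 to 0.0210 over the whole SD range).

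Only 0.125 × 0.0191 = 0.0024 of this is the baseline point itself; the rest comes through the correlated later values.

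**Scale.** If HC raised utility by an assumed 0.03 at every later visit, the gain would be 0.03 × 0.375 = 0.01125 QALY at 26 weeks and 0.03 × 0.875 = 0.02625 at 52 weeks. With SD 0.15, the one-SE shift is 53-72% and 41-60% of those gains. The percentages rise in proportion to the SD and halve if the gain is doubled.

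**The two wordings.** If the mean change in QALYs meant the area above each person's own baseline, the quantity would be QALY minus horizon × baseline utility. The two versions then differ by horizon × imbalance: 0.5 × 0.0191 = 0.0096 QALY at 26 weeks and 0.0191 at 52 weeks, whatever ρ is. The change version has slope −0.375(1 − ρ) or −0.875(1 − ρ) on baseline, so it overcorrects whenever ρ is below 1. Regression on baseline utility avoids both errors.

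**The case against.** A reader might infer that the protocol has chosen a raw, unadjusted QALY comparison. The article does not say so. Section {20b} says how each participant's QALYs are built and defines the ratio; an adjusted difference in means would fit that definition too. Section {20a} promises an analysis plan that is not shown, and covariates for incremental QALYs are the kind of detail such a plan may hold. The only stated policy on baseline adjustment favours it. A reader might also infer that the ICUR would be biased. Under 1:1 randomization it would not be, in expectation. Finally, every utility input above is assumed, and this is an additional analysis that leaves the SPPB comparison and the sample size untouched.

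Most of this stands, and it limits the point. It does not remove it. Section {20b} does more than defer: it defines the contrast for a primary economic outcome, in two wordings, and names no covariate. The {20a} rule cannot be carried over as worded. Someone following the article alone would compute an unadjusted difference in means.

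**Conclusion.** The point holds as an improvement to what {20b} states. Taken as written, the ICUR denominator is a difference in mean area-under-the-curve QALYs into which a chance baseline utility imbalance would carry. The harm is lost precision and an error conditional on the observed imbalance.

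The variance reduction of about 57-83% at 26 weeks and 52-81% at 52 weeks rests on equal SDs and equal between-visit correlations of 0.5-0.8; it does not depend on the size of the SD. The absolute shifts also depend on the assumed SD, and their comparison with a treatment effect on the assumed 0.03 gain, so those are illustrations of scale only.

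**What to change.** In Methods for additional analyses {20b}, and in the analysis plan before data release:

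1. State that incremental QALYs at 26 and 52 weeks are estimated by regressing each participant's QALYs on arm and baseline EQ-5D-5L utility.
2. State that this adjusted difference is the ICUR denominator and is used in any uncertainty analysis.
3. Show the unadjusted difference as a supplement.
4. Replace the reference to a mean change in QALYs with the adjusted difference in mean QALYs between arms, so that one contrast is defined throughout.

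The cost is a few sentences and one covariate already collected. Visits, sample size and the primary analysis do not change. If the analysis plan already says this, only the article's wording needs to be brought into line.

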### Methods in analysis to handle protocol non-adherence and any statistical methods to handle missing data {20c}

Missing outcome data will not be imputed since estimates from linear mixed models are fully efficient if the missing data are missing at random [63]. If we encounter more than 10% missing outcome data, we will consider plausible explanations for why the data may not be missing at random and assess the sensitivity of the results by fitting a joint model that incorporates non-ignorable dropout [64]. Missing covariate data will be multiply imputed assuming they are missing at random, unless there is a clear rationale for treating them otherwise.

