### Strategies to improve adherence to interventions {11c}

HC participants will manually track their weekly PA in a physical log. Health coaches will actively work with participants to help them adjust and modify their action plan to meet their PA goals.

To minimize attrition within the ED group, participants will receive a 1-h HC session and 2 follow-up HC phone calls upon completing the 52-week assessment. At this time, participants will receive access to the exercise intervention videos and manuals.

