### Sample size {14}

The sample size for this study is 290 participants, based on SPPB data published in the LIFE study that examined changes in SPPB scores based on changes in MVPA [6]. At 6 months, those in the highest quartile of MVPA change (i.e., > 43 min per week) experienced a mean improvement (calculated as 6 months minus baseline) of 1.21 in SPPB score with a SD = 0.98. A 0.5 difference in SPPB score is considered a clinically meaningful change [58]. Assuming at least 90% of our HC participants will increase their participation in MVPA by at least 50 min per week, and splitting the remaining 10% of HC participants equally among the 3rd quartile in MVPA change (mean SPPB change = 1.16) and the 2nd quartile in MVPA change (mean SPPB change = 0.89), we anticipate a mean SPPB improvement of 0.90 × 1.21 + 0.05 × 1.16 + 0.05 × 0.89 = 1.19 in the HC group. For the ED group, we assume the mean SPPB change will be similar to what was observed in the LIFE study control group [6]; we calculated this value to be 0.84 from the published data. Thus, the effect size for the SPPB outcome is (1.19 − 0.84)/0.98 = 0.36.

Using a two-tailed test alpha = 0.05, our estimated effect size requires a sample size of 246 participants (123 per group) in order to achieve 80% power, assuming the outcomes for all participants are independent. In principle, this sample size should be adjusted by a design effect (DE) to account for the nesting of participants within coaches in the HC arm and nesting of participants within cohorts in the ED arm. However, as noted in the description of the HC intervention, the ICC in a previous study was found to be only 0.0007 [17]. Together with an expected 15 participants per coach, the DE is only 1 + (15 − 1) × 0.007 = 1.01 which implies a negligible impact on the required sample size. No data are available on the ICC within ED groups, but we expect it to be low enough to also have negligible impact. Allowing for a 15% dropout rate leads to the sample size of 290 participants (i.e., 145/group).

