### Plans to promote participant retention and complete follow-up {18b}

Participants in the HC group will have regular communication from bi-monthly to monthly sessions with their BAP coach to promote retention and adherence to the intervention. Participants in the ED group will have the same structure of engagement with group education sessions to promote retention and adherence. Education session attendance will be incentivized by entering participants into a gift card drawing every other session. Throughout the study intervention and follow-up time frame, participants will receive monthly communication from study personnel to assess falls and other outcomes. In a previous study utilizing a similar HC protocol in adults with mild cognitive impairment, adherence rates to PA recommendations with ≥ 73% and attrition rates were ≤ 10.4% [59, 60].

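### The only planned check for non-random dropout depends on an undefined 10% threshold that does not measure a difference between arms

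*Protocol article*

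**What the plan says.** Section {20c} of the protocol article sets out the handling of missing outcomes. The main analysis relies on the mixed model: "Missing outcome data will not be imputed since estimates from linear mixed models are fully efficient if the missing data are missing at random". One check on that assumption follows, with a condition attached: "If we encounter more than 10% missing outcome data, we will consider plausible explanations for why the data may not be missing at random". Only then will the team "assess the sensitivity of the results by fitting a joint model that incorporates non-ignorable dropout". The section does not say whether the 10% is pooled or per arm, or which visit or outcome it refers to.

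Other sections bear on the point:

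- Sample size {14} inflates both groups by the same factor: "Allowing for a 15% dropout rate" takes 246 participants to 290, or 145 per group.
- Section {17a} says that participants cannot be blinded.
- Section {11c} offers the ED group coaching after the 52-week assessment, with the stated purpose "To minimize attrition within the ED group".
- Section {18b} describes retention measures for both groups ("Participants in the ED group will have the same structure of engagement with group education sessions to promote retention and adherence") and adds a gift card draw for attendance at education sessions.
- Section {20a} promises a statistical analysis plan before data are released.

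**The concern.** A mixed model without imputation gives a valid HC-ED contrast if outcomes are missing at random. If they are not, the error in the contrast depends on two things: the fraction missing in each arm, and how far the unseen outcomes lie from what the model predicts for them. A single missingness percentage captures neither. A low figure can hide a large imbalance, and a higher figure spread evenly over the arms can be nearly harmless.

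Unequal dropout is plausible here. Participants know their group, one arm receives individual coaching and the other group education, and the protocol takes retention steps specific to ED. If the imbalance arose with little dropout in total, the rule as written would not call for any check on the missing-at-random estimate. The undefined denominator adds a second difficulty, because whether the rule is met could be decided after the missingness is known.

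**Working it through.** **1. The plan's own figure.** From Sample size {14}: 246 / (1 − 0.15) = 289.4, rounded up to 290, or 145 per group. This reproduces. The planned effect is 1.19 − 0.84 = 0.35 SPPB points, with SD 0.98.

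**2. What the threshold lets through.** On a pooled reading, more than 10% of 290 means at least 30 participants, since 29/290 = 10.0% does not exceed 10%. So 29/145 = 20% missing in one arm and 0/145 in the other gives no check. On a per-arm reading, the rule would be met at 15 of 145 in either arm.

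**3. How likely the pooled trigger is.** P(X ≥ 30), with X binomial (290, p):

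- p = 15% (the planning figure): 99.2%
- p = 12%: 83%
- p = 10%: 45%
- p = 8%: 9%
- p = 5%: 0.02%

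**4. Size of the possible bias.** Let f be the fraction missing in an arm, and δ the amount by which the true mean of the missing outcomes differs from the missing-at-random prediction. The estimated HC − ED contrast is then off by f(ED) × δ(ED) − f(HC) × δ(HC). The protocol gives neither the split nor δ, so both are assumptions. The central value of δ is 0.5, which {14} takes as clinically meaningful; the range shown is 0.25 to 0.98 (one SD). All splits below total 29 missing, and δ is the same in both arms.

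| Missing, one arm v the other | Difference in f | Bias, δ = 0.25 | Bias, δ = 0.5 | Bias, δ = 0.98 |
|---|---|---|---|---|
| 29 v 0 | 29/145 = 0.200 | 0.050 (14% of 0.35) | 0.100 (29%) | 0.196 (56%) |
| 22 v 7 | 15/145 = 0.103 | 0.026 (7%) | 0.052 (15%) | 0.101 (29%) |
| 15 v 14 | 1/145 = 0.007 | 0.002 (0.5%) | 0.003 (1%) | 0.007 (2%) |

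The pooled missingness is 10.0% in every row, yet the bias at δ = 0.5 runs from 0.003 to 0.10.

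**5. Effect on the test in the worst case.** This is a rough two-sample calculation with 145 observed in one arm and 116 in the other: SE = 0.98 × √(1/145 + 1/116) = 0.122. A bias of 0.10 raises the two-sided type I error from 5% to 13.0%. If it runs against HC, power falls from 82% to 54%. For biases of 0.05 and 0.196, the type I errors are 6.9% and 36.2%, and the powers 69% and 24%.

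**6. Direction.** If most dropouts are in ED and would have done worse than predicted, the HC effect is understated. If they would have done better, it is overstated. Nothing in the protocol settles which.

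**The case against.** The strongest reply is that the plan's own dropout figure exceeds the threshold. At 15%, the joint model would almost certainly run, so the gap opens only if retention is better than planned. That stands, and it limits the point. It is also true that {20c} does not forbid a check below 10%, that the coming analysis plan could define the denominator, and that the splits and departures above are assumed. A departure of 0.5 points beyond what the model already predicts from observed data is not small. What remains is that {20c} states a rule rather than leaving the matter open, and an analysis plan faithful to it would carry the rule forward.

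A reader might infer three stronger things that the document does not support.

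- **That the protocol expects dropout to be concentrated in ED.** Section {11c} describes an incentive, not a forecast. Section {14} plans one common rate, and {18b} covers retention in both arms.
- **That the rule would fail even at 15% dropout.** If dropout accrues evenly to week 26 and then stops, missingness averaged over all four visits is (0 + 7.5 + 15 + 15)/4 = 9.4%. That figure counts the baseline visit, which {13} and {16c} place before allocation is made known. Over the three later visits it is (7.5 + 15 + 15)/3 = 12.5%, and the rule is met.
- **That one or two participants will decide whether the check is done.** The attrition of at most 10.4% cited in {18b} is an upper bound from an earlier study in adults with mild cognitive impairment. It is not this trial's planning figure.

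**Conclusion.** The point holds, with minor to moderate weight. The only stated analysis for non-random dropout is tied to a threshold with no defined denominator and no regard to arm. On a pooled reading, it can leave 20% v 0% missingness unexamined. Under an assumed 0.5-point departure, the 26-week contrast would shift by 0.10 points (29% of the planned effect) in that extreme case, and by about 0.05 (15%) for a 22 v 7 split, in either direction. These sizes rest on the pooled reading, the assumed splits and the assumed departure. The problem does not arise if dropout runs near the planned 15%, and unequal dropout is a plausible risk in an unblinded trial, not something the protocol predicts.

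**What to change.** In {20c}, delete the 10% condition. State that the joint-model sensitivity analysis will be carried out for SPPB in every case, with dropout modelled separately by arm, and that missing SPPB will be reported by arm and visit. A simple arm-specific delta analysis may be added. It is not in {20c} at present, but it is useful if an arm has too few dropouts for the joint model to be well determined.

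The cost is a short amendment to {20c}, carried into the analysis plan, and modest extra analysis time. The joint model is already planned. Sample size, data collection and the primary analysis do not change.
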